**Figure 1 F1:**
[figure not shown]
Study flow chart.

### Measurement of FFR

Coronary angiography will be performed with 6-French catheters at baseline and after the 4-week intervention. The FFR is the maximal achievable flow, which determines the functional capacity. The FFR is defined as the mean distal coronary pressure divided by the mean proximal coronary or aortic pressure during maximal hyperemia [46-48]. The measurements will be performed using a coronary pressure guide wire (Prime Wire, Volcano Corp., Rancho Cardova, CA, USA, or Radi Pressure Wire Certus, St. Jude Medical, Sweden). Maximal hyperemia will be achieved by intravenous application of adenosine, administered via a right femoral vein in dose of 140 μg/kg body weight/min.

Measurement of the FFR will be done after application of adenosine infusion for approximately 2 min when a steady state has been reached. Right atrial pressure will be measured via the femoral vein in a standard manner.

### Measurement of the coronary collateral circulation

The primary study endpoint (change in CBF) will be assessed by sensor-tipped guide wires during vessel occlusion with a balloon catheter for 1 min.

Therefore, a standard PCI balloon with a diameter 0.5 mm larger than the diameter of the target vessel is delivered via the FFR guide wire and will be inflated proximal to the coronary lesion within an angiographic healthy coronary segment with a low pressure of 4–6 atm to interrupt antegrade blood flow of the vessel during maximal hyperemia. Contrast dye is injected to show the interruption of the antegrade blood flow. During the measurement, the blood pressure of the target vessel distal to the coronary stenosis is continuously monitored as well as the systemic blood pressure.

To differentiate if the results after 4 weeks of therapy are due to CAD or physiological adaptations, the same measurements will be performed in a coronary vessel free of coronary stenosis (the reference vessel).

After 4 weeks of treatment, measurements will be repeated in the same coronary segments.

Cardiac catheterization as well as measurement of the CBF will be performed by three very experienced invasive cardiologists with expertise in hemodynamic analysis. Nevertheless, the procedure may carry some risks such as dissections of the coronary artery by the pressure wire, development of the thrombus burden, stroke or myocardial infarction during vessel occlusion. Application of adenosine intravenously can result in a complete atrioventricular block with short asystole.

### Assessment of clinical symptoms and patient treatment

All patients undergo detailed assessment of medical history as well as physical examination at baseline and after 1, 3, 6 and 12 months. In patients without known diabetes, an oral glucose tolerance test will be performed before inclusion.

At baseline, 1, 3, 6 and 12 months, the angina pectoris status will be documented according to CCS class 1–4 by a physician blinded to the treatment group. In addition, a symptom-limited bicycle ergospirometry and an echocardiography will be conducted.

An OMT is adjusted according to current clinical practice guidelines in each group at least 2 weeks before initial measurements were obtained. Statins, ß blockers, angiotensin-converting enzyme inhibitors or angiotensin-1 antagonists are obligatory. In addition, patients are treated with an antiplatelet therapy with aspirin 100 mg daily or, if the patient has undergone a previous PCI, a dual antiplatelet therapy will be administered according to current guidelines.

All patients enrolled in the study will be followed for 12 months. At any time during the study period, each patient can withdraw the informed consent. A patient with signs of clinically worsening symptoms will be thoroughly evaluated by the investigator, and if clinically indicated a PCI will be performed. In patients presenting with an acute coronary syndrome, a coronary angiography will be performed immediately, and the target lesion will be treated by PCI. The study will be discontinued for a given patient if continuing would result in a significant safety risk.

### Qualitative Comparative Analysis (QCA Analysis)

QCA measurements of the target lesion and the healthy reference coronary artery will be obtained at baseline and after 4 weeks respectively by two independent operators using the Medis Software (Medis Medical Imaging Systems, QAngio XA, version 7.2).

The following parameters will be measured: lesion lengths (mm), minimum/maximum lumen diameter (mm), target stenosis (%) and the diameter of the reference coronary artery at the location of FFR measurement (mm).

### Intravascular ultrasound examination (IVUS sub-study)

IVUS imaging with an analysis of the virtual histology of the coronary plaque has the potential to overt possible effects of the specific therapy of the study with respect to change in the plaque composition and plaque volume of the target lesion.

Therefore, an IVUS with virtual histology analysis will be performed at baseline and after 4 weeks of therapy. After measurement of the FFR and CBI, an Eagle Eye^R^ Gold Intravascular Ultrasound Imaging Catheter (Volcano Corporation, Rancho Cardova, CA, USA) will be inserted distal to the target lesion at a landmark side branch and pulled back via a motorized transducer pullback device for a length of at least 4 cm. ECG-triggered virtual histology is performed to analyze the tissue composition.

The details on IVUS image acquisition and analysis have been reported previously [49-53]. The percentage of atheroma volume, total plaque burden, minimal lumen area (mm^2^), lesion lengths (mm) and differentiation of plaque tissue (%) will be measured [54].

### Adenosine MR perfusion imaging (MRI sub-study)

A cine MRI and an adenosine perfusion MR will be performed at baseline, 4 weeks and 12 months. The aim of this sub-study is to investigate whether MR perfusion imaging can predict myocardial perfusion defects, collateral circulation, LV function and volumes after 4 weeks of exercise training compared to a sedentary control group.

Imaging will be performed with a 1.5-T scanner (Philips Intera CV, Best, The Netherlands) in a standard fashion. After 4 min of adenosine infusion, a perfusion sequence will be started according to a standard protocol. All measurements will be performed by blinded operators with excellent intra- and interobserver variabilities and excellent reproducibility. Exclusion criteria for the MRI sub-study are (1) severe claustrophobia, (2) implantable pacemaker and defibrillator, and (3) contraindications for adenosine (first and second degree AV block, sick sinus syndrome, long QT syndrome, asthma bronchiale).

### Exercise testing

All patients will perform a cardiopulmonary exercise test on a bicycle ergospirometer (Ergoline, Bitz, Germany) to determine the individual exercise capacity and the peak oxygen uptake (V0_2_ peak), angina threshold and ischemic threshold. The step protocol starts at 25 W and increases by steps of 25 W every 3 min. The Zan SpiroErgo 600 (Zan, Winkling, Austria) is used to measure breath-by-breath gas exchange levels of ventilation (E), oxygen uptake and carbon dioxide production (CO_2_). Important measured parameters are the exercise capacity (Watts), angina pectoris threshold, ischemic threshold, V0_2_ max/peak, time to discontinuation (T max) and time to anaerobic threshold (T RQ1). After 4 weeks, 3, 6 and 12 months, the test will be repeated.

### Exercise training program

Patients randomized in the IT group perform exercise training under supervision by experienced physicians and exercise physiologists four times daily for 30 min, five times a week for a total of 4 weeks. The training program is intended to be a high-intensity training with partial IT up to 95% of the individual ischemia-/angina-free exercise capacity.

Patients randomized in the MT group will undergo a multimodal lifestyle intervention in a specialized hospitalized rehabilitation unit. These patients will exercise 6–8 sessions per day (20 min each) under close medical supervision at a maximum level of 70% of their individual angina-/ischemia-free exercise threshold. Additionally, they will be in lifestyle modification as well as individual physiotherapeutic therapies.

Patients assigned to the sedentary control group receive an OMT and are encouraged to carry out regular ET according to current guidelines (2–3 sessions per week, 20–30 min each). They are supervised by their general practitioner.

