**Discussion:**

The trial investigates whether ET for 4 weeks increases the CBF in patients with significant CAD compared to a sedentary control group. It also examines the impact of two intensities of ET on the CBF as well as the histological plaque composition. The trial started recruitment in June 2009 and will complete recruitment until June 2012. First results are expected in December 2012 (4-week follow-up), final results (12-month long-term secondary endpoint) in December 2013.

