### Hypothesis

Therefore, the *Leipzig **EX**er**CI**se **T**raining versus M**E**dical Management* (EXCITE) trial is designed to test the hypothesis that a 4-week ET therapy in addition to OMT can increase coronary CBF compared to baseline measurements. In a second step analysis, the impact of different ET intensities (IT versus MT) on the change of CBF will be elucidated.

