## Methods/design

### Study objectives

The EXCITE study is a three-armed, randomized, prospective, open-label, controlled trial in patients with stable CAD and a significant coronary artery stenosis of at least one major epicardial vessel. The severity of the coronary stenosis is assessed by measurement of the FFR. An FFR of ≤0.75 of at least one coronary stenosis is feasible for study inclusion. The aim of the study is to investigate the efficacy of 4 weeks of intensive exercise training in addition to OMT on the amount of CBF compared to a sedentary control group with OMT only. It will determine if exercise training is superior to standard medical therapy in increasing the CBF. Moreover, the Excite trial wants to demonstrate the superiority of a strategy of intensive interval exercise training compared to moderate-intensity exercise training. The trial is a proof-of-concept study and registered under http://www.clinicaltrial.gov: NCT01209637.

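### The IT versus MT contrast is presented as showing the effect of exercise intensity, but the MT arm is described with co-interventions not listed for IT, so it can only compare two whole programmes

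*Protocol article*

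**What the plan says.** Two places in the protocol article make intensity the object of the IT–MT contrast. The Hypothesis section says that in a second analysis step "the impact of different ET intensities (IT versus MT) on the change of CBF will be elucidated". The Discussion paragraph of the abstract says: "It also examines the impact of two intensities of ET on the CBF as well as the histological plaque composition". The Study objectives section is worded differently: the trial "wants to demonstrate the superiority of a strategy of intensive interval exercise training compared to moderate-intensity exercise training".

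The Exercise training program section describes what each arm receives.

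- **IT:** supervised training "four times daily for 30 min, five times a week for a total of 4 weeks", described as "high-intensity training with partial IT up to 95% of the individual ischemia-/angina-free exercise capacity". No other component is listed, and the setting is not stated.
- **MT:** "Patients randomized in the MT group will undergo a multimodal lifestyle intervention in a specialized hospitalized rehabilitation unit". Training is 6–8 supervised sessions of 20 min per day, at no more than 70% of the angina- or ischemia-free threshold. Lifestyle modification and individual physiotherapy are added.

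The article does not list the MT additions for IT, and it does not comment on the difference. The main Discussion section raises the lack of blinding and of a power calculation, but not this.

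**The concern.** A contrast isolates intensity only if the two arms are alike in everything else that could move the outcome. As described, MT is moderate exercise plus other active components, while IT is exercise alone. Randomization balances the patients. It does not remove differences that belong to the assigned treatment.

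What is at stake is the sentence the trial may write at the end. If IT and MT show similar changes in collateral flow, the stated aim invites the conclusion that intensity does not matter. If MT does better, it invites the conclusion that moderate intensity is preferable. Either result could come from the lifestyle or physiotherapy components. The same applies to plaque composition, which the abstract puts under the intensity question, and to lipid and glucose status, which are secondary endpoints that lifestyle modification could plausibly affect directly.

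**Working it through.** The article gives no figure for this point, so there is none to reproduce. The check sets the two arm descriptions side by side, computes daily exercise time, and asks what the contrast identifies.

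**Arm descriptions (Exercise training program; MT format from Background, Exercise training and CAD)**

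| Feature | IT | MT |
|---|---|---|
| Intensity ceiling | 95% of ischemia-/angina-free capacity | 70% of angina-/ischemia-free threshold |
| Format | partly interval | continuous |
| Sessions per day | 4 × 30 min | 6–8 × 20 min |
| Setting | not stated | inpatient rehabilitation unit |
| Lifestyle modification | not listed | yes |
| Individual physiotherapy | not listed | yes |

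**Daily exercise time** = sessions per day × minutes per session.

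- IT: 4 × 30 = 120 min.
- MT, low end: 6 × 20 = 120 min.
- MT, high end: 8 × 20 = 160 min.
- MT/IT ratio: 120/120 = 1.00 to 160/120 = 1.33.

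Session number and length differ throughout. Daily minutes are equal at the low end of MT and higher for MT above it.

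**What the contrast identifies.** Let I be the effect of the higher intensity of IT on the change in collateral flow, and P the effect of the MT-only components. Treat the effects as additive for illustration, and leave format and session structure aside. The randomized comparison then estimates D = I − P. The design gives D but cannot separate I from P.

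- If D = 0, then I = P. Intensity may have no effect, or a benefit fully offset by the extra components.
- If D < 0, then I < P. I may be negative, zero or positive.
- If D > 0 and the extra components do no harm (P ≥ 0), then I = D + P ≥ D > 0. The extra components could not have produced the IT advantage, though the size of I remains unknown.

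The ambiguity is therefore greatest for a null result or an MT advantage. Putting format back in, even an IT advantage could not be credited to intensity alone, because IT is partly interval training and MT is continuous.

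**The case against.** The strongest reply is that the article already treats the contrast mostly as one between programmes. The title and Background speak of modalities, the abstract's Methods/design of two training programmes, and the main Discussion of finding the programme that works best. The Study objectives sentence claims superiority of a strategy. This stands: that sentence is not an instance of the error, and the fault is confined to the intensity wording in the Hypothesis section and the abstract's Discussion. It also shows that the remedy uses language the article already has. It does not remove the mismatch, because those two places still promise an answer about intensity.

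A reader might infer more than the documents support:

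- **That training volume differs.** Daily minutes can be equal. A weekly excess beyond the daily ratio needs an assumed number of MT training days. At 5 days MT is 600–800 min/week against 600 for IT (ratio 1.00–1.33). At 7 days it is 840–1,120 (ratio 1.40–1.87).
- **That leaving out the MT days per week is a fault.** A journal article may leave this to the full protocol.
- **That inpatient MT is set against outpatient IT.** The IT setting is not stated.
- **That a pooled exercise-versus-control estimate is contaminated.** The Data and statistical analysis section names a Kruskal-Wallis test for the primary endpoint and defines no pooled analysis.
- **That a result in either direction is equally uninterpretable.** If the extra components help, they work against IT, so they would not explain an IT advantage.

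It is also fair to say that nothing in the article indicates how far 4 weeks of lifestyle modification or physiotherapy would move collateral flow.

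**Conclusion.** The concern holds in a limited form. The Hypothesis section and the abstract attribute the IT–MT contrast to exercise intensity, while the Exercise training program section lists lifestyle modification and individual physiotherapy for MT and not for IT. These components alone are enough to prevent attribution to intensity, even if minutes and setting were identical. The different session format adds to this. Total exercise time is not needed for the argument.

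A reader might go further and infer that the IT–MT comparison is invalid. The documents do not support that: allocation is randomized, and the comparison of the two whole programmes stands. Only its stated interpretation fails.

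The size of the problem cannot be given in units of collateral flow, because the article supplies no effect size for the extra components. The only computable quantity is daily exercise time, 1.00 to 1.33 times that of IT. The verdict assumes that the arm descriptions are complete in what they list. If the full protocol gives IT the same lifestyle and physiotherapy components, the main confounding goes and the article's description needs correcting.

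**What to change.** 1. In the Hypothesis section and the abstract's Discussion, restate the second objective as a comparison of two training programmes, in line with the wording already used in the abstract's Methods/design and the main Discussion. Remove intensity as the attributed cause there and in the planned conclusion.
2. State the MT-only components as a limit on interpretation, in particular for a null result or an MT advantage.
3. Reconcile the intensity wording with the arm descriptions in the Exercise training program section. This review takes no position on either training schedule.
4. Where records of the supervised sessions exist, report achieved minutes and intensity by arm beside the IT–MT result. The article mentions supervision but not such records, so this is conditional. The table would describe the programmes; it would not restore attribution to intensity.

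The cost is a few sentences and, if records exist, one descriptive table. Allocation, sample size and the primary test do not change. The downside is that the trial gives up the claim to show an effect of intensity.

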### Laboratory values and biomarkers

Blood samples will be taken and analyzed at baseline, at 1, 3, 6 and 12 months. Routine measurements of lipid and glucose metabolism will be performed. In addition, the amount of circulating endothelial progenitor cells (EPCs) will be quantified by flow cytometry as recently described [55,56].

Asymmetric dimethylarginine (ADMA) and endostatin will be measured using a commercial available ELISA kit (for ADMA: Immundiagnostik AG, Bensheim, Germany; for Endostatin: Antigenix American Incorporation) following the manufacturer’s instructions.

The association between interleukin-6 and tumor necrosis factor-alpha to the CBF will be determined.

### Long-term follow-up

Follow-up will be conducted after 3, 6 and 12 months as ambulatory visits at our institution. In case of any events, these will be verified by hospital charts or direct contact with the treating physician.

### Data and statistical analysis

In the absence of randomized trials and lacking data regarding ET and its impact on the collateral blood supply, a power calculation was not possible. Therefore, the Excite trial is designed to be a proof-of-concept study.

Categorical variables are presented as frequencies and percentages, continuous variables as means and standard deviations (SD), or medians and interquartile ranges for variables with skewed distributions. The primary endpoint will be analyzed according to the intention-to-treat principle using the Kruskal-Wallis test. In addition, event rates in all of these three treatment arms will be estimated (95% CI), and the time-to-event rates will be described using the Kaplan-Meier method. The secondary endpoints (Table 3) will be analyzed by appropriate methods according to data type to compare the three treatment arms. If statistically possible, pre-defined subgroup analyses will be performed including patients’ gender, presence of diabetes, amount of pre-existing CBF and FFR of the target lesion at baseline.

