### Primary and secondary outcomes

The primary study endpoint of the EXCITE trial is the change in the coronary CBF index after 4 weeks of therapy among the three treatment groups (Table 1).

**Table 1 T1:** Primary and secondary endpoints

**Primary**	**Change in CBI after 4 weeks of treatment**
Secondary	1. Change in plaque morphology by virtual
	histology at 4 weeks as assessed by IVUS
	2. Change in myocardial perfusion at 4 weeks and
	12 months as assessed by adenosine MRI
	3. MACE at 1, 3, 6 and 12 months
	4. Hospitalization due to cardiovascular causes
	5. Change in atherosclerotic parameters (hs-CRP,
	ADMA, endostatin, EPC, ox LDL, cytokines,
	adiponectine), lipid status and glucose status
	6. Change in exercise capacity (ergospirometry) and
	V0_2_ peak

The secondary endpoints include the change in the tissue composition of the target lesion after 4 weeks of exercise training compared to optimal medical therapy only.

Other secondary endpoints are displayed in Table 1. To confirm a potential advantage by long-term follow-up, a 12-month follow-up will be performed in the course of the secondary endpoint evaluation.

Safety assessment includes bleeding complications related to the invasive measurement of the CBF according to the GUSTO criteria [45], stroke and renal failure.

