### Study examinations

After the patient has provided written informed consent, a cardiac catheterization with a clinical indication is performed. In case of a coronary artery stenosis >50%, a measurement of FFR will be performed. Only target vessels that are feasible for PCI with a minimum diameter of ≥2 mm will be included. Therefore, patients with a coronary stenosis of <2 mm will be excluded. Patients with an FFR of ≤0.75 will be enrolled in the study and randomly assigned by a computerized system in a 1:1:1 ratio to one of the three treatment groups (20 patients per group) with stratification according to age and sex. The study flow chart is shown in Figure 1.

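### The one named primary test, a three-group Kruskal-Wallis test, does not by itself establish either superiority aim, and the hypothesis is worded against baseline instead of control

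*Protocol article*

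**What the plan says.** All references are to the protocol article.

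- **Data and statistical analysis** gives one method for the primary endpoint: "The primary endpoint will be analyzed according to the intention-to-treat principle using the Kruskal-Wallis test". It names no contrast, test order, significance level or multiplicity rule.
- **Primary and secondary outcomes** defines that endpoint as "the change in the coronary CBF index after 4 weeks of therapy among the three treatment groups".
- **Study objectives** sets two directional aims. The first: "It will determine if exercise training is superior to standard medical therapy in increasing the CBF". The second is that the trial "wants to demonstrate the superiority of a strategy of intensive interval exercise training compared to moderate-intensity exercise training".
- **Hypothesis** says the trial tests whether "a 4-week ET therapy in addition to OMT can increase coronary CBF compared to baseline measurements", and continues: "In a second step analysis, the impact of different ET intensities (IT versus MT) on the change of CBF will be elucidated".
- **Study examinations** allocates patients "in a 1:1:1 ratio to one of the three treatment groups (20 patients per group").

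The abstract's Discussion and the Conclusion return to a comparison with the sedentary control group.

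**The concern.** The primary question appears in three forms: among three groups, exercise against control (followed by one programme against the other), and against baseline. The named test answers only the first. The conclusions the trial wants to draw belong to the second.

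Kruskal-Wallis is a global, non-directional test on 2 degrees of freedom. A small p-value says that at least one arm differs from another. It does not identify the arm or the direction, and it gives no effect estimate. If it is the only stated analysis, the contrast that carries the headline claim can be chosen after the results are known.

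The baseline wording is a separate weakness. A rise in collateral flow within the trained patients could come from medical therapy, repeat measurement or regression to the mean. Read literally, the hypothesis could be met with no difference from the randomized control arm.

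**Working it through.** **1. Inputs.** Three arms of 20 give 3 × 20 = 60, which agrees with the stated total. The article gives no effect size, SD, significance level or power, and says that a power calculation was not possible, so there is no power figure to reproduce. What follows assumes normally distributed changes, differences in units of the SD of change, and a two-sided 5% level.

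**2. Stated aims against the named test.**

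| Stated question | Comparison needed | Answered by Kruskal-Wallis alone? |
|---|---|---|
| Do the three groups differ in change? | Global | Yes |
| Is exercise superior to medical therapy? | Exercise against control, with direction | No |
| Is IT superior to MT? | IT against MT, with direction | No |
| Is there an increase from baseline? | Within-arm change | No |

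**3. Does the global p-value tell the situations apart?** Simulation of 20,000 trials, 20 per arm, one pattern of 1 SD differences at a time:

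| True pattern | Kruskal-Wallis rejects |
|---|---|
| No difference | 4.9% |
| IT and MT both better than control | 88% |
| Only IT better | 88% |
| Only MT better | 88% |

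The rejection rate is the same although the right conclusions differ. In the second row IT is not superior to MT. In the last row MT is superior to IT, the reverse of the second aim.

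**4. Can Kruskal-Wallis serve as a gate?** Yes. With three arms, if any two of the three pairwise null hypotheses are true, all three arms are equal. Every intersection of pairwise nulls is therefore the global null, which Kruskal-Wallis tests at 5%. Pairwise tests at 5% each after a significant gate form a closed procedure, and familywise error stays at 5%.

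**5. Power of the gated pairs and of a pooled alternative.** Same set-up, rank tests:

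| True pattern | Kruskal-Wallis | Pooled exercise (40) vs control (20) | Gated IT vs control | IT vs MT |
|---|---|---|---|---|
| Both programmes +0.8 SD | 70% | 80% | about 60% | true difference is zero |
| Only IT +0.9 SD | 80% | 31% to 32% | 72% | 71% to 72% after the Kruskal-Wallis gate; 23% to 25% after a pooled first step |

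In the first row, gated MT vs control also has about 60%, by symmetry.

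**6. What 20 per arm can detect.** With 80% power, two-sided 5% and the normal approximation, the detectable difference is (1.960 + 0.842) × √(1/n₁ + 1/n₂) SD.

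- One pair, 20 vs 20: 2.802 × √(1/20 + 1/20) = 2.802 × 0.3162 = 0.89 SD.
- Pooled, 40 vs 20: 2.802 × √(1/40 + 1/20) = 2.802 × 0.2739 = 0.77 SD.
- At 2.5% these become 0.97 and 0.84 SD.

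The single-pair figure ignores the gate, which lowers power somewhat.

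**The case against.** The strongest reply is that the test and the endpoint agree. The endpoint is a comparison among three groups, and Kruskal-Wallis is the standard global rank test for that. This stands: the conflict is with the aims and the hypothesis, not with the endpoint definition.

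A second reply is that the Hypothesis section announces a second step, and that follow-up contrasts, their order and their levels are commonly left to an analysis plan. This stands in part. Such contrasts may exist in a document not shown, and their absence alone would be no finding. But the article itself fixes one global test and also says that the trial will determine two directional superiorities. The baseline wording is a statement, not an omission.

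A third reply is the proof-of-concept label. It explains the missing power calculation, but Study objectives still uses superiority language.

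Four stronger readings are tempting and are not supported:

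- *A significant result is worthless for both aims.* It shows that at least one arm differs, and contrasts can then address the aims.
- *The test is faulty because it also rejects when exercise is harmful, or when IT and MT differ while their average equals control.* Any two-sided test rejects under harm. With both programmes worse by 0.8 SD, a pooled test rejects in 80% of trials, against 69% for Kruskal-Wallis. In the other case the arms do differ, so rejection is correct.
- *The trial will declare success from a paired test within the exercised arms.* No such test is named, and other sections frame the aim against control.
- *The exercise arms should be pooled first.* Nothing in the article says they will be, and pooling loses much power if only one programme works.

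**Conclusion.** The point holds as a mismatch within the published text. The named test matches the endpoint definition but does not by itself establish exercise over medical therapy or IT over MT. The hypothesis as worded could be met without any difference from control. This should be fixed, but it does not invalidate the design: the named test is a sound first step, and what is missing is the stated link from it to the claims.

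That logic needs no numerical assumption. The simulated rates and detectable differences rest on normal changes, 20 analysed patients per arm, the SD multiples shown and a two-sided 5% level. None of the effect sizes, the SD or the level comes from the article.

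**What to change.** 1. Under Data and statistical analysis, keep Kruskal-Wallis as the global gate and state its level (two-sided 5% is assumed here).
2. If the gate is significant, test IT vs control, MT vs control and IT vs MT at 5% each. Add that this controls familywise error because there are exactly three arms.
3. Rest all superiority claims on these contrasts, programme by programme. Report each with an estimate and 95% confidence interval, whether or not the gate is passed.
4. Reword the Hypothesis section so that exercise training is expected to give a greater change in CBF than control. Make within-arm change from baseline descriptive.

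The cost is wording in the article and the analysis plan, with no added patients or measurements. The statistical downside is small: if both programmes work equally (0.8 SD assumed), each contrast with control has about 60% power, against 80% for a pooled contrast. In return, the IT vs MT comparison and a benefit confined to one programme remain detectable.
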